##### fMRI preprocessing

2.5.2.4

All fMRI preprocessing and statistical analyses will be conducted using Statistical Parametric Mapping (SPM; version 8 or later) implemented in MATLAB (MathWorks, Natick, MA, USA). Preprocessing will follow a standardized pipeline:

Slice Timing Correction: Adjustment for temporal differences in slice acquisition, performed prior to realignment for interleaved sequences.Realignment (Motion Correction): Correction for head motion using rigid-body transformation; six motion parameters will be estimated and included as nuisance regressors.Co-registration: Alignment of functional images to individual T1-weighted structural images for accurate anatomical localization.Spatial Normalization: Transformation of structural images into Montreal Neurological Institute space, with parameters applied to functional images.Spatial Smoothing: Application of a Gaussian kernel (full width at half maximum [FWHM] = 8 mm) to improve signal-to-noise ratio and meet statistical assumptions.

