The proposed pathway from recitation to gut microbiota modulation is mediated through autonomic nervous system regulation. Focused, rhythmic vocalization reduces hypothalamic–pituitary–adrenal (HPA) axis reactivity and enhances vagal tone, thereby attenuating stress-driven gut dysbiosis (Jabbari Shiadeh et al., 2025). Sustained psychological stress has been shown to alter neurotransmitter release and disrupt intestinal epithelial homeostasis by blocking protective vagal nerve barrier effects, shifting microbial composition toward pro-inflammatory profiles (Ningthoujam et al., 2021). Conversely, mind–body practices that enhance vagal tone are associated with healthier gut microbiota diversity and reduced pro-inflammatory bacteria. The mechanistic link between gut microbiota and brain plasticity operates primarily through microbial metabolites, as emerging evidence highlights the critical role of the gut-brain axis, a complex bidirectional network involving neural, endocrine, immune, and metabolic pathways (Tsai et al., 2025). Within this framework, gut microbiota has been shown to influence blood–brain barrier integrity, neuroplasticity, and cognitive function through the production of short-chain fatty acids, modulation of neurotransmitter precursors, and regulation of systemic inflammation (Agirman and Hsiao, 2021; Zhang et al., 2023). For instance, gut bacteria produce butyrate, acetate, and propionate, which cross the blood–brain barrier and upregulate the CREB/BDNF signaling pathway, promoting neuronal repair, memory consolidation, and synaptic plasticity, while suppressing neuroinflammation via inhibition of MAPK and NF-κB (Qian et al., 2022). In parallel, microbial tryptophan metabolism yields indole derivatives and kynurenine pathway intermediates that modulate serotonin synthesis and glutamatergic signaling — both critical for hippocampal neuroplasticity (Connell et al., 2022). Recent advances in whole-blood metabolomics have further identified disease-associated metabolic signatures in individuals with dementia (Teruya et al., 2021), underscoring the potential of metabolic profiling as a tool for early detection. These findings collectively suggest that alterations in the gut-brain axis may occur in the preclinical stages of cognitive decline. However, a direct causal link between classical recitation and modulation of the gut microbiome has not yet been established in any interventional trial, and whether cognitive training prevents or delays cognitive decline by protecting gut microbiota composition and metabolic profiles, particularly in individuals with SCD, has not been systematically investigated. Therefore, decoding how cognitive interventions modulate the degenerative interactions of gut-brain axis will generate significant impacts on preventive medicine.

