##### MRI acquisition protocol

2.5.2.2

MRI data will be acquired using a 3.0 Tesla scanner (GE Signa Architect, Milwaukee, WI, USA) equipped with a 40-channel head coil. Both structural and functional imaging data will be collected. High-resolution three-dimensional T1-weighted images will be obtained using either spoiled gradient recalled echo (3D-SPGR) or inversion recovery-prepared SPGR sequences, with isotropic spatial resolution of 1 × 1 × 1 mm^3^. These images will be used for anatomical localization, co-registration, spatial normalization, and region-of-interest (ROI) definition. Functional MRI (fMRI) data will be acquired using T2-weighted echo-planar imaging sequences with whole-brain coverage. Imaging parameters will include: repetition time (TR) = 2000 ms, echo time (TE) = 35–60 ms (depending on optimization), flip angle = 90°, matrix size = 64 × 64, field of view ≈ 224 × 224 mm^2^, slice thickness = 4.0–4.4 mm with a 0.4 mm interslice gap, and voxel size ≈ 3.5–3.6 × 3.5–3.6 × 4.4 mm^3^. A total of 32 axial slices will be acquired in interleaved order.

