For the neuroimaging analyses, task-related regressors will be convolved with the canonical hemodynamic response function, and motion parameters will be included as nuisance covariates. A high-pass filter of 128 s will be applied to remove low-frequency drift. At the single-subject level, voxel-wise GLM analyses will be performed to identify task-related activation patterns. Contrasts of interest (e.g., recitation versus resting baseline) will be evaluated using directional T-contrasts. At the group level, individual contrast maps will be entered into second-level random-effects models. Directional two-sample T-tests will be used for between-group comparisons, and conditions with similar activation patterns may be combined to enhance statistical power. Statistical significance will be set at *p* < 0.05, corrected for multiple comparisons using the false discovery rate (FDR) at the voxel level. For exploratory analyses, an uncorrected threshold of *p* < 0.001 may be applied. Extracted effect sizes from predefined ROIs will be further analyzed using Statistical Product and Service Solutions (SPSS). One-way analysis of variance will be used to assess condition-related differences, while Spearman’s rank-order correlation will evaluate associations between neural activation and clinical variables (e.g., years of education and Cognitive Reserve Index questionnaire (CRI-q) scores). Statistical significance will be defined as *p* < 0.05.

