Practically, the two approaches also differ in delivery. Conventional cognitive training is typically administered as discrete, algorithmically adaptive trials on an individual basis, with difficulty calibrated by software in response to real-time performance. Recitation is self-paced and continuous, often delivered in a group or instructor-guided setting, with dosage and repetition flexibly determined by the participant’s progress rather than by automated adjustment. This difference in implementation, combined with the use of culturally familiar material, gives recitation greater ecological validity, as it more closely resembles real-world language and memory processes than computerized drills and may support more sustained engagement. In addition to these conceptual and practical distinctions, the two approaches are also hypothesized to differ physiologically. Within the stress-axis framework, the rhythmic vocalization and breath regulation inherent in recitation are hypothesized to engage vagal and HPA-axis pathways, offering a candidate physiological mechanism — distinct from standard training paradigms — through which behavioral intervention could influence stress-related neuroplasticity and gut-brain signaling.

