Collectively, the following theoretical models: cognitive reserve, neural compensation, and stress-axis modulation, provide the mechanistic foundation for the present trial. While multiple potential mechanisms may underlie the effects of classical recitation on cognitive function, our primary hypothesis is that classical recitation training will be associated with greater change in resting-state functional connectivity within the hippocampal-default mode network than controls, consistent with intervention-induced neuroplasticity in memory-relevant circuits. Our secondary hypothesis proposes that the stress-axis modulation pathway, whereby recitation-induced enhancement of vagal tone and attenuation of HPA axis reactivity diminish stress-related gut dysbiosis, consequently fostering the production of beneficial microbial metabolites and neuroplasticity. Exploratory hypotheses include associations between classical recitation and shifts in gut microbiota composition and in circulating metabolomic profiles. By integrating behavioral training with multimodal biological measurements, including neuroimaging and peripheral biomarker analyses, this study seeks to bridge cognitive neuroscience theory with measurable physiological outcomes in individuals with subjective cognitive decline.

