Consistent with the hypothesis-generating nature of this pilot research, study outcomes are organized within a predefined inferential hierarchy. The primary outcome is designated as the principal efficacy endpoint and will serve as the main basis for evaluating intervention-related effects. The secondary outcome is pre-specified *a priori*; however, given the limited sample size typical of pilot studies, findings will be interpreted as supportive and hypothesis-generating rather than definitive. EEG, gut microbiota, and metabolomic measures are designated as exploratory outcomes. These measures are not powered for confirmatory inference and are intended primarily to generate preliminary effect-size estimates and identify candidate biomarkers for future adequately powered confirmatory trials.

Based on these findings, we anticipate that the primary outcome of this pilot trial is intervention-induced change in resting-state fMRI activation within the left medial temporal region, encompassing the hippocampus and parahippocampal gyrus, from baseline (T0) to post-intervention assessment at 6 months (T1). Increased resting-state fMRI activation in the left medial temporal region following recitation training is interpreted as reflecting enhanced cognitive reserve — the brain’s capacity to sustain normal cognitive function despite underlying neurodegenerative burden — consistent with the compensatory scaffolding framework of cognitive aging (Reuter-Lorenz and Park, 2014). We anticipate that the intervention group will demonstrate significantly greater increase in left medial temporal region activation compared to controls, with the effect expected to be more pronounced in participants with lower educational attainment — consistent with a compensatory neural response in individuals with lower a priori cognitive reserve (Stern et al., 2020).

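### The stated fMRI pipeline names no correction for cardiac or respiratory signal, although the protocol hypothesises that training changes vagal tone, so a resting-state arm difference could be partly physiological

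*Protocol article*

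**What the plan says.** **Pipeline.** Section 2.5.2.4 (fMRI preprocessing) lists five steps: slice timing, realignment, co-registration, normalisation and smoothing. Its only nuisance terms come from realignment: "six motion parameters will be estimated and included as nuisance regressors". Section 2.5.2.5 (Statistical analysis) repeats that "motion parameters will be included as nuisance covariates" and adds "A high-pass filter of 128 s will be applied to remove low-frequency drift". Section 2.5.2.2 gives "repetition time (TR) = 2000 ms". The article mentions no pulse or respiration recording, no white-matter or CSF regressors, no component-based denoising and no low-pass filter. Heart rate and respiration are neither outcomes nor covariates.

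**Mechanism.** The Introduction states "Focused, rhythmic vocalization reduces hypothalamic–pituitary–adrenal (HPA) axis reactivity and enhances vagal tone". Section 3.1 adds that "the rhythmic vocalization and breath regulation inherent in recitation are hypothesized to engage vagal and HPA-axis pathways", and its secondary hypothesis includes "recitation-induced enhancement of vagal tone and attenuation of HPA axis reactivity diminish stress-related gut dysbiosis".

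**Outcome.** Section 3.3 gives the primary outcome as "intervention-induced change in resting-state fMRI activation within the left medial temporal region", from baseline to 6 months, and reads an increase as greater cognitive reserve. The primary hypothesis in section 3.1 concerns resting-state connectivity between the hippocampus and the default mode network, and treats a larger change than in controls as consistent with neuroplasticity. The control group is non-active.

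**The concern.** The BOLD signal responds to breathing and heart rate as well as to neural activity. In many trials this adds noise that is similar in both arms. Here the protocol's own mechanism gives a reason why it might not be similar: if training raises vagal tone, autonomic state could differ between arms at the post-intervention scan.

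The usual protections would not remove such a difference. Randomisation balances what exists before training, and this would be caused by training. Baseline adjustment fails for the same reason, and assessor blinding does not act on the signal. A resting scan also has no task contrast to help separate neural from systemic signal.

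What is at stake is the meaning of the outcome that section 3.3 puts first, and the effect size that the pilot hands to a later definitive trial. As written, the analysis could not tell the primary (neural) hypothesis from a vascular by-product of the secondary (vagal) one.

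**Working it through.** **The plan's own figure.** The only calculated sample size is 383 per group (section 2.3: d = 0.18, one-tailed, alpha 0.05, power 0.80). It reproduces: the noncentral t gives power 0.8006 at 383 and 0.7997 at 382. It does not bear on this point, because it belongs to a hypothetical neuropsychological primary outcome and did not set the target of 60.

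**Step 1: does the stated filter remove physiological signal?**

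- Sampling frequency: fs = 1/TR = 1/2 s = 0.5 Hz, so the highest resolvable frequency is 0.25 Hz.
- High-pass cut-off: 1/128 s = 0.0078 Hz. Signal above this is kept, and no upper cut-off is stated.
- A frequency f appears at |f − fs × round(f/fs)|.

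The resting rates below are assumptions; the documents give none.

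| Source | Rate per min | f (Hz) | Appears at (Hz) | Above 0.0078 Hz? |
|---|---|---|---|---|
| Breathing | 6 | 0.100 | 0.100 | yes |
| Breathing | 12 | 0.200 | 0.200 | yes |
| Breathing | 18 | 0.300 | 0.200 | yes |
| Breathing | 20 | 0.333 | 0.167 | yes |
| Heart | 55 | 0.917 | 0.083 | yes |
| Heart | 60 | 1.000 | 0.000 | no |
| Heart | 70 | 1.167 | 0.167 | yes |
| Heart | 75 | 1.250 | 0.250 | yes |
| Heart | 80 | 1.333 | 0.167 | yes |

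Over the heart rates shown, the filter catches cardiac signal only within about 0.0078 × 60 = 0.47 beats/min of 60. Otherwise the signal stays in the retained band.

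**Step 2: what could a physiological difference do?** Let b be an arm difference in the region-of-interest measure, in SD units, that is entirely physiological, with no neural effect. Assume a single test with 30 per arm and one-sided alpha 0.05 (section 2.5.2.5 plans directional group comparisons). The rejection probability comes from the noncentral t with 58 degrees of freedom and noncentrality b × √(30/2). For b = 0.3 the noncentrality is 0.3 × 3.873 = 1.16.

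| b (assumed) | False-positive rate |
|---|---|
| 0 | 5.0% |
| 0.1 | 10.3% |
| 0.2 | 19.0% |
| 0.3 | 31.0% |
| 0.5 | 60.6% |

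One way to think about b is r × δ, where r is the correlation of the uncorrected measure with physiology and δ is the arm difference in physiology in SD units. With r assumed at 0.2 to 0.4 and δ at 0.3 to 0.8, b runs from 0.2 × 0.3 = 0.06 to 0.4 × 0.8 = 0.32. Neither r nor δ is in the documents.

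The table takes b in the predicted direction. If the artefact ran the other way, the rate would fall below 5% and a true effect would be masked.

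**The case against.** **Silence is not exclusion.** The article does not say that motion parameters are the only nuisance terms, and an imaging manual or analysis plan, not shown, may contain physiological correction. That possibility stands. But the pipeline is set out step by step, down to the kernel width and filter cut-off, and motion is the only nuisance source named, twice. Followed as stated, it leaves the outcome exposed.

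**The model in 2.5.2.5 is written for task data.** This is fair: the sentences on motion covariates and the filter sit in a description of task regressors, so they are weaker evidence about resting data. The preprocessing section, however, introduces its steps for fMRI generally, and the article states no other noise removal for resting scans.

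**A lasting change in breathing is not stated.** A reader might infer that the protocol expects trained participants to breathe more slowly in the scanner, so that bias is certain. The text does not support that. It places breath regulation within recitation itself and hypothesises a change in vagal tone. Carry-over to a silent rest scan is an inference.

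**The size is assumed.** A reader might also set the illustrative 0.06 to 0.32 SD against d = 0.18 and conclude that the bias matches the planned effect. That comparison fails, because 0.18 was not the basis for the 60 participants.

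**The trial is exploratory.** Sections 2.3 and 2.5 describe fMRI as exploratory, and section 3.1 uses the language of association. Yet section 3.3 makes its primary outcome the main basis for judging intervention effects.

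**Correction may remove signal of interest.** Vagal change lies on the hypothesised pathway, so a rule allowing a plasticity claim only after correction would not be neutral. This is why both results should be shown.

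**Conclusion.** The point holds as a possibility that the stated analysis leaves open; it is not a demonstrated bias. Two parts are firm. The pipeline names no cardiac or respiratory correction, and its high-pass filter does not supply one at a 2 s repetition time under ordinary resting rates. The article also hypothesises an autonomic effect of training while planning to read a resting-state arm difference as plasticity or cognitive reserve.

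That physiology will actually differ between arms at 6 months is conditional on the protocol's own mechanism and on its carry-over to the rest scan. Size and direction are unknown from the documents; the false-positive rates above show sensitivity to assumed values and are not estimates. The change is worth making before scanning starts, because pulse and respiration that were not recorded cannot be recovered later.

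**What to change.** 1. In section 2.5.2.4, add for resting-state data nuisance regressors made of principal components of the white-matter and CSF signals. They are computed from images already acquired.
2. Report the primary region-of-interest result with and without these regressors.
3. Where pulse and respiration sensors are already available at the scanner, record both during the fMRI runs at baseline and 6 months, and report the arm difference as a sensitivity analysis.
4. In section 3.3, state that if the result does not survive correction, a physiological explanation cannot be excluded, and do not interpret it as plasticity or cognitive reserve.

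If a fuller imaging document already specifies such correction, stating it in 2.5.2.4 covers item 1.

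**Cost.** A processing change, a small loss of temporal degrees of freedom, and possible removal of some signal on the hypothesised vagal pathway; reporting both results lets readers see that trade-off. Tissue components are only a proxy for recorded physiology, hence item 3. The documents do not say whether sensors are available, so that item is conditional.

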##### Statistical analysis

2.5.2.5

Statistical analyses will be conducted within the framework of the general linear model (GLM). For the primary clinical outcomes (e.g., subjective cognitive measures, neuropsychological test scores), a linear mixed-effects model will be used to handle the repeated-measures structure of the data throughout baseline, post-intervention, and follow-ups, with time, group, and group × time interaction as fixed effects, and subject as a random effect. This approach naturally accommodates missing data under the missing-at-random (MAR) assumption without requiring complete cases. The primary analysis will follow the intention-to-treat principle, including all randomized participants regardless of adherence or dropout, with missing values handled using multiple imputation based on baseline characteristics and available follow-up data. A per-protocol sensitivity analysis will also be conducted, restricted to participants who complete at least 80% of the intervention sessions. Covariates to be included in adjusted models will comprise age, sex, years of education, and baseline cognitive scores, selected *a priori* for their known associations with cognitive outcomes in SCD populations.

For the neuroimaging analyses, task-related regressors will be convolved with the canonical hemodynamic response function, and motion parameters will be included as nuisance covariates. A high-pass filter of 128 s will be applied to remove low-frequency drift. At the single-subject level, voxel-wise GLM analyses will be performed to identify task-related activation patterns. Contrasts of interest (e.g., recitation versus resting baseline) will be evaluated using directional T-contrasts. At the group level, individual contrast maps will be entered into second-level random-effects models. Directional two-sample T-tests will be used for between-group comparisons, and conditions with similar activation patterns may be combined to enhance statistical power. Statistical significance will be set at *p* < 0.05, corrected for multiple comparisons using the false discovery rate (FDR) at the voxel level. For exploratory analyses, an uncorrected threshold of *p* < 0.001 may be applied. Extracted effect sizes from predefined ROIs will be further analyzed using Statistical Product and Service Solutions (SPSS). One-way analysis of variance will be used to assess condition-related differences, while Spearman’s rank-order correlation will evaluate associations between neural activation and clinical variables (e.g., years of education and Cognitive Reserve Index questionnaire (CRI-q) scores). Statistical significance will be defined as *p* < 0.05.

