## Introduction

1

Dementia, a progressive neurodegenerative condition strongly associated with aging, imposes substantial social, economic, and familial burdens worldwide. Its prevalence is projected to continue rising, posing significant challenges to global public health systems (Liu et al., 2025). In Asia, the increase has been particularly pronounced: from 1990 to 2021, the incidence, prevalence, and mortality of Alzheimer’s disease (AD) and related dementias increased by 244.73, 250.44, and 297.34%, respectively (Guo et al., 2025). These alarming trends underscore the urgent need for early identification and intervention strategies targeting preclinical stages of cognitive decline.

Subjective cognitive decline (SCD) was formally conceptualized in 2014 to describe a self-reported experience of cognitive deterioration in individuals who perform normally in objective and standardized neuropsychological tests (Jessen et al., 2020). The trajectories of SCD are heterogeneous, ranging from reversible or stable forms to progressive phenotypes that evolve into mild cognitive impairment (MCI) and eventually dementia (Jessen et al., 2020). A meta-analysis reported that approximately 14% of individuals with SCD developed dementia over a four-year follow-up period (Mitchell et al., 2014). Despite its clinical significance as a potential preclinical stage of neurodegeneration, no pharmacological treatments are currently approved specifically for SCD (Smid et al., 2022).

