Following completion of the initial six-month intervention phase, participants will be given the option to voluntarily continue recitation practice. The selection of a six-month intervention period is informed by the MEMO+ (Méthode d’Entrainement pour Mémoire Optimale) protocol developed by Sylvie Belleville and colleagues (Bier et al., 2015). Later studies from the same research team have demonstrated that participants receiving structured cognitive training exhibited significant improvements in memory recall performance, with effects persisting for at least 6 months post-intervention (Belleville et al., 2018). Furthermore, long-term follow-up over 5 years revealed that individuals who had undergone cognitive training experienced a slower decline in delayed memory performance and Montreal Cognitive Assessment (MoCA) scores compared with control groups (Belleville et al., 2024). These findings underscore the sustained benefits and potential long-term impact of continuous cognitive training.

Additional support for the selected intervention duration is derived from studies examining other forms of cognitively engaging activities. For example, interventions involving structured calligraphy practice have demonstrated that extending training duration over a six-month period leads to significant alterations in functional brain connectivity (Lee et al., 2024). Specifically, increased connectivity has been observed between the medial prefrontal cortex (mPFC) and right lateral temporal cortex (LTC), mPFC and right inferior parietal lobe (IPL), left hippocampal formation (HF) and right LTC, as well as between the left HF and right IPL (Lee et al., 2024). These findings suggest that prolonged engagement (6 months) in cognitively demanding tasks may induce measurable neuro-modulatory effects at the network level.

Taken together, a 6-month intervention period represents a balanced design choice: it is sufficiently long to allow for detectable behavioral and neurobiological changes, yet not so prolonged as to compromise participant adherence. Accordingly, outcome assessments will be conducted at baseline (time of recruitment), immediately after the six-month intervention, and at one-year and two-year follow-ups, with annual assessments thereafter until participants are no longer able to complete evaluations. The study will be conducted at China Medical University Hospital, primarily within the outpatient clinics of the Departments of Neurology or Psychiatry.

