### Statistical methods

2.6

The primary efficacy analysis will be conducted using generalized linear mixed-effects models to analyze repeated measures data, with adjustment for relevant covariates. Microbiome analyses will be performed using DESeq2 to identify differentially abundant taxa and linear discriminant analysis effect size to detect potential microbial biomarkers. Metabolomic data will be analyzed using partial least squares discriminant analysis, and pathway enrichment analysis will be conducted using the MetaboAnalyst platform. Multi-omics integration will be performed using Spearman correlation-based network analysis and causal mediation analysis to investigate regulatory mechanisms along the gut-brain axis. Multiple comparisons will be corrected using FDR, with a threshold of *q* < 0.05. All statistical analyses will be conducted using R (version 4.4.0; R Core Team, 2024) and SPSS (version 29.0; IBM Corp., Armonk, NY, USA), with statistical significance set at *p* < 0.05.

Given the inherent complexity and multi-layered nature of multi-omics data, if the aforementioned methods are insufficient for comprehensive analysis, we will collaborate with the institutional Artificial Intelligence Center affiliated in our hospital to implement advanced analytical approaches. These may include machine learning, network-based modeling, and partial least squares regression, among others, to construct predictive models that characterize causal or associative relationships between biological markers and clinical outcomes (e.g., cognitive function and depression). The predictive performance of different models will be systematically compared.

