
Epidemiological evidence has consistently identified modifiable lifestyle factors associated with reduced risk of cognitive decline and dementia. A landmark study published in *The Lancet Neurology* demonstrated that rich social networks, engagement in mental activities, and regular physical activity represent three major protective factors against cognitive decline, Alzheimer’s disease, and dementia in older adults. Among these, mental activities were particularly associated with preserved verbal intelligence and reduced rates of cognitive deterioration. Proposed mechanisms include the cognitive reserve hypothesis, the vascular hypothesis, and the stress hypothesis (Fratiglioni et al., 2004).

The cognitive reserve framework posits that lifelong intellectual enrichment enhances neural efficiency, capacity, and flexibility, thereby allowing individuals to better tolerate age-related neuropathology before clinical symptoms emerge. Substantial interindividual variability exists in cognitive aging trajectories; for example, some individuals in their eighties may demonstrate superior cognitive performance compared to middle-aged adults (Cabeza et al., 2018). A 20-year longitudinal study involving 3,777 older adults concluded that education was a key determinant of this variability, with higher educational attainment associated with delayed clinical manifestation of cognitive impairment by approximately 7 years (Amieva et al., 2014). These findings support the concepts of cognitive maintenance and reserve, suggesting that education and sustained mental engagement enhance neuroplasticity and increase resilience to neuropathological burden. Importantly, cognitive reserve is not static. It accumulates through education and occupational complexity during midlife but may decline in later life depending on physical health, psychosocial stress, and ongoing cognitive engagement (Cabeza et al., 2018). Structured cognitive training may therefore serve as a modifiable intervention to reinforce reserve mechanisms during aging. In the present study, fMRI will be employed to detect subtle alterations in neural activation patterns and network connectivity associated with recitation-based cognitive training.

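### Clinical and neuropsychological outcomes: a single subject random effect over open-ended annual follow-up assumes equal rates of change; the error is small to 2 years and grows with each added visit

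*Protocol article*

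**What the plan says.** Section 2.5.2.5 of the protocol article sets the model: "For the primary clinical outcomes (e.g., subjective cognitive measures, neuropsychological test scores), a linear mixed-effects model will be used". It covers the "repeated-measures structure of the data throughout baseline, post-intervention, and follow-ups". The model terms are then listed in full: "with time, group, and group × time interaction as fixed effects, and subject as a random effect". No random slope and no within-subject covariance structure is named.

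Section 2.6 returns to the repeated-measures analysis without adding a random structure: "The primary efficacy analysis will be conducted using generalized linear mixed-effects models to analyze repeated measures data, with adjustment for relevant covariates".

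Section 2.1 puts the first two assessments at baseline and at the end of the training period. Later ones come "at one-year and two-year follow-ups, with annual assessments thereafter until participants are no longer able to complete evaluations". The visit list therefore has no fixed end.

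On how individuals change, section 1 says: "The trajectories of SCD are heterogeneous, ranging from reversible or stable forms to progressive phenotypes". Section 3.1 adds: "Substantial interindividual variability exists in cognitive aging trajectories".

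**The concern.** A random intercept as the only random term implies constant variance and the same correlation between any two visits, whether six months or five years apart. That holds only if everyone in an arm changes at the same rate apart from visit-to-visit noise, and the article's own account of this population says otherwise.

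When slopes vary, the spread of individual change widens with time, but the model uses one pooled within-person variance. That variance is too small for slope and late-visit comparisons and too large for the 6-month comparison. A chance excess of fast decliners in one arm can then look like a long-term effect, while an effect at the end of the intervention gets too wide an interval. The trial's stated product is effect sizes for a later trial, so misstated intervals would be carried forward.

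**Working it through.** **The plan's own figure.** The article gives no operating figure for the mixed model. Its only power figure for neuropsychological scores (section 2.3: 383 per group, d = 0.18, one-sided 5%, power 0.8006) is for a two-sample t-test. It reproduces exactly with the noncentral t, but it does not bear on the covariance question.

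**Inputs.**
- From the article: 30 per arm (2.3); visits at 0, 0.5, 1 and 2 years, then yearly (2.1).
- Assumed: intercept SD 0.8 and residual SD se = 0.6, so baseline variance is 0.64 + 0.36 = 1; slope SD sb = 0.1, 0.2 or 0.3 baseline SD per year; complete data; no true arm effect.
- The 5-year horizon is illustrative. The article fixes no analysis time beyond the visit list.

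**Formulas.** Let T be the number of visits, S the sum of squared deviations of the visit times from their mean, and V = S/(T − 1).
- Change from baseline to time t: true variance 2se² + t²sb²; variance used by the model 2(se² + sb²V).
- Person-level slope: true variance sb² + se²/S; variance used by the model se²/S + sb²/(T − 1).
- With r = √(true/model), the actual two-sided error is about 2Φ(−t_crit/r).

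Visits to 2 years: S = 2.1875, V = 0.729. Visits to 5 years: S = 20.93, V = 3.488.

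**Worked case, sb = 0.3, visits to 5 years.** The model uses 2(0.36 + 0.09 × 3.488) = 1.348 at every visit.
- 6 months: true 0.72 + 0.25 × 0.09 = 0.7425; r = 0.742; error 0.8%.
- 5 years: true 0.72 + 25 × 0.09 = 2.97; r = 1.484; error 18.5%.
- Linear slope: true 0.09 + 0.36/20.93 = 0.1072; model 0.0172 + 0.0150 = 0.0322; r = 1.825; error 28.1%.

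**Rejection rates at nominal 5%** (closed form; joint test by simulation):

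| Test | sb 0.1 | sb 0.2 | sb 0.3 |
|---|---|---|---|
| To 2 years: linear group × time | 5.3% | 6.6% | 8.5% |
| To 2 years: 2-year contrast | 5.2% | 6.3% | 8.0% |
| To 2 years: 6-month contrast | 4.7% | 4.2% | 3.5% |
| To 2 years: joint visit × group | 4.8% | 5.1% | 5.1% |
| To 3 years: linear group × time | 6.2% | 9.8% | 14.2% |
| To 5 years: linear group × time | 10.1% | 20.4% | 28.1% |
| To 5 years: 5-year contrast | 7.6% | 13.4% | 18.5% |
| To 5 years: 6-month contrast | 4.0% | 2.1% | 0.8% |
| To 5 years: joint visit × group | 5.2% | 6.8% | 9.0% |

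The linear rows and the visit-contrast rows belong to different fits: time as a linear covariate, or time as a visit factor.

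**Checks.**
- Simulation (40,000 trials per setting) agrees with the closed form to within 0.5 percentage points. With no slope variation every test rejects about 5%. Allowing the variance of change to differ by visit, or comparing person-level slopes, keeps about 5% throughout.
- REML fits with 36 per arm and 20% dropout, at sb/se = 0.4 (800 trials per setting), give to 5 years: slope test 24.2%, 5-year contrast 15.8%, 6-month contrast 2.0%. To 2 years they give 10.0%, 8.2% and 4.5%.
- If follow-up years are counted from the end of intervention (0, 0.5, 1.5, 2.5 years), sb/se = 0.4 gives 8.7% for the slope, 7.8% for the last visit and 3.3% at 6 months.

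**Power at 6 months**, for an assumed 0.5 SD effect from 6 months on, stated model (visit factor) against visit-specific variance:
- Visits to 5 years: 49% against 61% (sb 0.2) and 35% against 60% (sb 0.3).
- Visits to 2 years: 59% against 61%, and 56% against 60%.

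**The case against.** The strongest reply is that naming subject as a random effect is ordinary shorthand. The article does not say intercept only, and an analysis plan that is not shown could add a slope or a residual covariance. That is possible. But section 2.5.2.5 writes out the fixed and random parts and the visits they cover, and the usual reading of what it writes is a random intercept. This is a stated model that conflicts with the article's description of the population, not merely an absent detail.

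Other points stand and limit the finding:
- The slope SD is assumed. At 0.3 per year the total variance at 5 years is 1 + 25 × 0.09 = 3.25, so the outcome SD grows about 1.8-fold; that is the upper end of my range, not an estimate.
- Over the visits the article names, the joint test is essentially correct and the other tests move by a few points at most.
- The article does not say whether time is linear or categorical, and no 5-year analysis is specified.
- Section 2.3 already says that the neuropsychological outcomes are underpowered and need cautious reading.

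A reader might infer that one and the same test both over-declares late effects and under-declares the 6-month effect. The article does not support that: with linear time there is no separate 6-month test, and with categorical time the joint test stays between about 5% and 9% even to 5 years. A reader might also infer that the main imaging result is compromised. It is not: section 2.5.2.3 schedules fMRI at baseline and 6 months only, and with two visits and complete data a random intercept and an unstructured covariance give the same test of change.

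**Conclusion.** The concern holds for the clinical and neuropsychological outcomes only. As written, the model rules out the between-person variation in rate of change that the article itself describes. It rests on reading the random term as a random intercept and on an assumed slope SD of 0.1 to 0.3 baseline SD per year.

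On those terms the consequence to 2 years is minor. It becomes material as annual visits accumulate: either a slope test that rejects far too often (linear time), or late contrasts that are too liberal beside a 6-month contrast that is too conservative (categorical time). It should be corrected in the wording; it does not undermine the trial's 6-month fMRI comparisons.

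**What to change.** In section 2.5.2.5:
- Estimate the 6-month group contrast from baseline and 6-month data alone, or from a model whose variance may differ by visit, so that later visits do not set its standard error.
- For the long-term group × time analysis, replace the single subject effect with a random intercept and a random slope on time since baseline. Where visits are few, for example to 2 years, an unstructured covariance with Kenward-Roger degrees of freedom is an alternative.
- State whether time is a visit factor or linear.

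Apply the same rule to the repeated-measures models in section 2.6.

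The cost is wording, with no new data. An unstructured matrix has 4 × 5/2 = 10 parameters for four visits but 7 × 8/2 = 28 for seven, which is too many to lead with for about 60 people and an open visit list. A random intercept and slope need four variance parameters, including the residual, instead of two. Late-visit intervals will be wider, which is the correct width if slopes vary.
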